#### FC Analysis

Differential brain regions obtained by ALFF or ReHo analysis, regions of interest, and differential brain regions will be selected, and FC will be calculated. An FC plot for each participant will be obtained by DynamicBC using the sliding window method. We will select a window length of 50 times of repeat (time of repeat: 100 seconds) with a window overlap of 98% (step size of 1 time of repeat) to calculate the FC for each participant. The FC plots for each participant will be calculated within each window to generate a series of FC plots. The coefficient of variation of the FC map is calculated to measure the temporal variability of intrinsic brain activity. Finally, the FC variability of all the participants will be transformed into standardized *z* scores to enhance the normality of the data by subtracting the mean of each voxel and dividing by the standard deviation [30].

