### Outcome Measurements

We will present the trial results by using both objective and subjective indicators. fMRI will be used for the main measurements, reflecting the changes in the participants’ brain structure and functional changes. Short-Form McGill Pain Questionnaire (SF-MPQ), pressure pain thresholds (PPTs), and the Oswestry disability index (ODI) will indicate the degree of pain and lumbar dysfunction and will be used for secondary outcome measurements.

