### Statistical Analysis

Statistical analysis will be conducted using SPSS 26.0 statistical software. Count data will involve the ratio of the sex and age variables compared between the 2 groups via the *χ*^2^ test of the 4-fold table or the Fisher test. The SF-MPQ scores, PPTs, and ODI scores are the rank data. Therefore, the Mann-Whitney *U* test will be used for the intergroup comparison, and the Wilcoxon symbolic test will be applied for the intragroup comparison. Paired 2-sided *t* test will be used to assess the difference in ALFF and ReHo between the 2 groups. In addition, Pearson correlation coefficients will be used to estimate the connection between the seed region and all of the voxels within the whole brain separately based on the patients. Statistical significance will be set at *P*<.05 (2-sided).

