In addition, we add neuroimaging observations based on objective indicators. Previous neuroimaging studies have shown that patients with LDH can show changes in brain structure and function. Liu et al [43] found that compared with the control group, patients with LDH had considerably longer typical path lengths in the brain network, as well as worse clustering coefficients, global efficiency, and local efficiency. Another systematic review [44] noted that in patients with LDH, the medial prefrontal cortex, cingulate cortex, amygdala, and insular lobe are more active. Pain-relief areas are less active, and the FC in pain-related areas is changed. Mei et al [45] reported that LDH may involve altered FC in several brain regions as well as decreased excitability in sensory motor areas during tasks and increased activity in the sensory-motor network during resting states. Therefore, brain structural changes and dysfunction caused by long-term pain afferent signals may be the key factors for pain associated with LDH.

Neuroimaging technology also provides an objective basis for Tuina’s cerebral mechanism in treating LDH. Li et al [46] found that after receiving Tuina treatment, the hypothalamus, left nucleus accumbens, and left amygdaloid of patients with LDH were excited, while the left anterior cingulated gyrus was inhibited. Yuan et al [47] discovered that after Tuina treatment, the brain functional activity in patients with LDH was mainly inhibited and the inhibited areas were located in the right side of the prefrontal cortex and cerebellum and that Tuina has the ability to alter the default mode network’s functionality in patients with LDH, which may help explain some of the intervention’s analgesic effects [12]. The above findings suggest that brain function regulation may be an important factor affecting Tuina’s effect on pain regulation. Therefore, we designed this study as a clinical randomized controlled trial to compare the effectiveness of Tuina with that of traction combined with TENS in patients with LDH and to investigate the cerebral mechanism of Tuina in LDH treatment by using fMRI. The results of this trial will provide a visual basis for the clinical application of Tuina in the treatment of LDH and provide a solid foundation for Tuina therapy research.

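### The coefficient of variation of raw sliding-window FC falls as connectivity gets stronger, so it cannot by itself support a claim about temporal variability

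*Protocol article*

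**What the plan says.** The FC Analysis section takes its seeds from the ALFF and ReHo results and from regions of interest. It then describes a dynamic method: "An FC plot for each participant will be obtained by DynamicBC using the sliding window method". The window is 50 repetition times (100 seconds), moved one repetition time at a time. The windowed maps are reduced to one summary: "The coefficient of variation of the FC map is calculated to measure the temporal variability of intrinsic brain activity". That summary is carried forward: "Finally, the FC variability of all the participants will be transformed into standardized *z* scores to enhance the normality of the data". The section does not name the correlation estimator used inside each window, and it mentions no Fisher transformation.

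The Statistical Analysis section adds: "Pearson correlation coefficients will be used to estimate the connection between the seed region and all of the voxels within the whole brain". It mentions neither windows nor variability there. The only fMRI measures that it ties to a comparison are ALFF and ReHo: "Paired 2-sided *t* test will be used to assess the difference in ALFF and ReHo between the 2 groups".

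Outcome Measurements treats imaging as a whole: "fMRI will be used for the main measurements, reflecting the changes in the participants’ brain structure and functional changes". FC is not singled out as an outcome. The Introduction and the Abbreviations list use FC and dFC as separate terms, but the FC Analysis section calls its dynamic measure simply FC.

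**The concern.** The plan attaches a specific interpretation, variability over time, to a statistic with mean connectivity in its denominator. If one treatment strengthens a connection more than the other, the CV at that connection will be lower in that arm even when neither treatment changes how much the connection fluctuates. A team following the plan could then report that Tuina altered the dynamics of brain activity when only the strength of a connection had changed.

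This matters because imaging is the main measurement and the trial's stated aim is the cerebral mechanism of Tuina. Greater stability and greater strength are different mechanistic claims.

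A smaller, related point is that the article does not say how the Pearson step in Statistical Analysis relates to the windowed measure. It is therefore unclear whether the full-run FC needed to detect this problem will be produced at all.

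**Working it through.** **Inputs from the protocol.** Repetition time 2 s and 300 timepoints (Primary Outcome Measurement); window of 50 repetition times, step 1 (FC Analysis); 30 evaluable patients per group (Sample Size Calculation, before the dropout allowance); two-sided 0.05 (Statistical Analysis).

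**The plan's own figures reproduce.** Window: 50 × 2 s = 100 s. Overlap: (50 − 1)/50 = 98%. Run: 300 × 2 s = 10 min. Number of windows: 300 − 50 + 1 = 251, of which 300/50 = 6 do not overlap.

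**Formula.** With r_w the correlation in window w, CV = SD(r_w)/|mean(r_w)|. If the true correlation r is constant, the spread of r_w is sampling error only, roughly proportional to 1 − r². Then CV is roughly proportional to (1 − r²)/r:
- r = 0.4: 0.84/0.4 = 2.10
- r = 0.5: 0.75/0.5 = 1.50, ratio to r = 0.4 of 0.71
- r = 0.6: 0.64/0.6 = 1.07, ratio to r = 0.4 of 0.51

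So the CV should fall by about 29% and 49% with no change in dynamics.

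**Simulation.** Assumptions not in the protocol: one connection, Gaussian series, constant true r, and a 0.01–0.08 Hz band (the protocol gives this band for ALFF, not for FC). Medians over 2,000 simulated pairs per setting:

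| True r | Mean windowed r | SD over windows | CV |
|---|---|---|---|
| 0.2 | 0.198 | 0.210 | 1.09 |
| 0.3 | 0.295 | 0.200 | 0.69 |
| 0.4 | 0.395 | 0.187 | 0.48 |
| 0.5 | 0.495 | 0.168 | 0.34 |
| 0.6 | 0.591 | 0.146 | 0.25 |
| 0.7 | 0.691 | 0.116 | 0.17 |

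From 0.4 to 0.5 the unrounded CV goes from 0.477 to 0.339, a ratio of 0.71, as the formula predicts. The mean rises by a factor of 0.495/0.395 = 1.25 and the SD falls by a factor of 0.168/0.187 = 0.90. Most of the change therefore comes from the denominator. The raw SD also shrinks, because a correlation is bounded. The SD of Fisher-z transformed windowed r does not: its mean was 0.236–0.239 across the values simulated.

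**Effect on a comparison of arms.** 30 per arm, independent t test at 0.05, no dynamics in either arm. The between-patient SD of true connectivity on the Fisher-z scale is not in the protocol, so a range is shown. Rejection rates:

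| Between-patient SD | CV, 0.4 v 0.5 | CV, 0.4 v 0.6 | SD of Fisher-z, both |
|---|---|---|---|
| 0 | 82% | 99% | about 5% |
| 0.1 | 54% | 91% | about 5% |
| 0.2 | 19% | 56% | about 5% |
| 0.3 | 8% | 31% | about 5% |

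The CV has a long upper tail, so these rates carry some simulation error. Repeat runs at an SD of 0.2 gave 16–20% and 53–66%. They should be read to within about ten points.

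**Does the planned z-scoring help?** If each voxel is centred and scaled by constants common to all patients, the transformation is linear and the test at that voxel is unchanged. It does not remove the dependence on mean FC.

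**The case against.** A reader might infer that the protocol contradicts itself: FC as temporal variability in FC Analysis, FC as plain connection strength in Statistical Analysis, hence two FC outcomes under one name. The text does not establish this. FC Analysis computes FC within windows without naming an estimator, and the Pearson coefficient in Statistical Analysis can be read as supplying it. That section does not call the quantity static, a strength or an outcome, and it attaches no between-group test to it. A separate full-run analysis is an equally possible reading, so the sections need a linking sentence. But the confusion of strength with dynamics would remain if the Pearson sentence were deleted, because it comes from the CV's denominator.

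A second objection concerns size, and it stands. The highest rejection rates require every patient in an arm to have the same true correlation, which is not realistic. With plausible spread between patients the rates fall steeply, to 8% at the low end shown. The simulation also covers one connection, while the planned analysis is whole-brain, and the frequency band is borrowed from ALFF. The direction of the artefact survives all of this, but no single rate can be given for this trial.

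A third objection is that the Introduction motivates dynamic FC directly, citing changed dFC variance after Tuina, so measuring dynamics is a legitimate choice. That also stands. General background on altered FC does not oblige the trial to make static FC its main FC outcome.

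Finally, details of FC testing may sit in an analysis plan that is not shown, and their absence is not counted here. The point concerns a metric that the article does fix.

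**Conclusion.** The point holds in this form: the CV of raw windowed FC is a poor measure of temporal variability because it moves with mean connectivity. Following the plan as written can present a difference in strength as a difference in dynamics.

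The distortion of the metric is firm. Raising a constant correlation from 0.4 to 0.5 lowers the median CV by about 29%, and both the formula and the simulation show it. The consequence for a trial comparison depends on assumptions. With 30 per arm it runs from 82% down to 8% rejection for 0.4 v 0.5, and from 99% down to 31% for 0.4 v 0.6, as the assumed between-patient Fisher-z SD goes from 0 to 0.3. These rates presuppose a real difference in strength between arms. They are not the false-positive rate when the arms do not differ at all.

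The relation between the Pearson step and the windowed measure is an ambiguity to clear up, not a proven contradiction. The change is worth making before analysis but does not threaten the trial as a whole.

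**What to change.** 1. In FC Analysis, replace the coefficient of variation with the SD over windows of Fisher-z transformed windowed r, and call the result dFC.
2. Report the full-run Fisher-z Pearson FC (all 300 timepoints) for the same seed and voxels beside it. A difference at a given connection can then be read against any difference in strength there. Static FC need not become the main FC outcome.
3. In Statistical Analysis, add one sentence saying whether the Pearson coefficient is the within-window estimator or this separate full-run analysis.

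The cost is a few lines of text and one more map per scan, from data already being collected. No new scans or patients are needed. A small downside is that results will be less directly comparable with earlier work that used the CV. The Abstract says that no data analysis has been performed, so the change can still be made in advance.

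Suggested wording: *Dynamic FC (dFC) is the standard deviation over windows of the Fisher-z transformed windowed Pearson correlation. Full-run Fisher-z FC for the same seed and voxels is reported alongside, and a dFC difference is interpreted as a change in temporal variability only in the light of it.*

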Recently, some scholars have used fMRI technology to study the central mechanism of Tuina in the treatment of LDH pain and obtained some positive results. For example, Zhou et al [18] found that patients with LDH showed abnormal brain ALFF and regional homogeneity (ReHo) values, which were altered after Tuina manipulation. Patients with LDH showed decreased ReHo in the left orbital part of the middle frontal gyrus, decreased dynamic FC (dFC) variance between the left orbital part of the middle frontal gyrus and the left fusiform, and increased dFC variance in the left orbital inferior frontal gyrus and left precuneus. Tuina therapy positively altered the ReHo and dFC values, making the brain activities in patients with LDH similar to those in healthy controls [12].

In recent years, although many studies [12,19] have provided evidence on the central brain mechanism of Tuina analgesia by using fMRI technology, relatively few studies have explored the central mechanism of Tuina in the treatment of LDH. Therefore, we designed a randomized controlled trial to explore the potential cerebral mechanism of Tuina analgesia by using fMRI.

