### Primary Outcome Measurement

The fMRI examination will be performed in the Imaging Department of the Rehabilitation Hospital affiliated to Fujian University of Traditional Chinese Medicine. The first fMRI scan will be performed 1 day before the start of treatment, and the second fMRI scan will be performed within 6 hours after the last intervention. The fMRI data will be collected by a 3.0 Tesla magnetic resonance scanner (MAGNETOM Prisma 3.0T, Siemens) with 64-channel phase-array head coils. During the acquisition process, participants will be required to close their eyes, relax, stay awake, keep their heads fixed as far as possible, and not perform thinking activities. We will perform fMRI at the beginning and end of the experiment.

To acquire the structural images, we will use the following parameters. The T1-weighted imaging scan parameters are as follows: time of repeat=2200 ms, time of echo=2.48 ms, flip angle=8°, field of view=230 mm×230 mm, matrix=256×256, resolution=0.98×0.98×1 mm^3^, slice number=160, and slice thickness=1.0 mm. The functional images will be acquired using the following parameters: time of repeat=2000 ms, time of echo=30 ms, flip angle=90°, field of view=230 mm, matrix=64×64, resolution=3.6×3.6×3.6 mm^3^, slice number=37, slice thickness=3.6 mm, and scan time=10 minutes for 300 timepoints.

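### Dynamic FC variability is measured by a coefficient of variation of a signed correlation, which is unstable where mean FC is near zero and confuses FC strength with variability elsewhere

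*Protocol article*

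**What the plan says.** Under FC Analysis, the protocol article computes FC in sliding windows for each participant and then reduces the series of maps to one variability map: "The coefficient of variation of the FC map is calculated to measure the temporal variability of intrinsic brain activity". The windows are fixed by "We will select a window length of 50 times of repeat (time of repeat: 100 seconds) with a window overlap of 98" per cent, with a "step size of 1 time of repeat".

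The resulting variability values are then to be "transformed into standardized *z* scores to enhance the normality of the data", by centring and dividing by a standard deviation.

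The Statistical Analysis section says what FC is: "Pearson correlation coefficients will be used to estimate the connection between the seed region and all of the voxels within the whole brain". The article mentions no absolute value, Fisher transformation or restriction to voxels with non-trivial mean FC. It names a test for ALFF and ReHo but none for FC variability.

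**The concern.** A CV is interpretable for a positive quantity that stays away from zero. A Pearson correlation lies between -1 and 1, and a whole-brain seed map can include voxels whose mean over windows is close to zero or negative. Three problems follow from the text alone.

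- **Instability.** As the mean approaches zero the ratio grows without bound and takes whichever sign the mean happens to have. A negative amount of variability has no meaning.
- **Confounding.** With the same fluctuation over windows, a weaker mean gives a larger CV. If treatment alters FC strength only, the CV still moves, and a strength effect would be reported as a variability effect.
- **Normalisation.** Subtracting a mean and dividing by an SD does not change the shape of a distribution, so the stated purpose of the z-score is not met.

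fMRI is the primary outcome and dynamic FC is one of its three described metrics, so the interpretation of one part of the mechanistic result is at stake.

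**Working it through.** **Inputs from the article.** The functional series has 300 timepoints in 10 minutes (Primary Outcome Measurement: "time of repeat=2000 ms, time of echo=30 ms"). The window is 50 repeats and the step is 1 repeat (FC Analysis). There are 38 participants per group (Sample Size Calculation).

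**Assumed inputs.** The true seed-to-voxel correlation rho is not given, so it was varied. The 0.01-0.08 Hz band is stated for ALFF only; it was applied to FC, and unfiltered data were also run.

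**The plan's own figures.** Overlap = (50 - 1)/50 = 98%. Window = 50 x 2 s = 100 s. Scan = 300 x 2 s = 10 min. All three agree with the article. Number of windows = 300 - 50 + 1 = 251.

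**Step 1: behaviour of the CV.** Gaussian seed and voxel series were simulated with a constant true rho, 20,000 pairs per value. CV = SD of windowed r / mean of windowed r.

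| rho | Median SD of r | Median absolute CV | 99th percentile absolute CV | CV negative | 99th percentile, unfiltered |
|---|---|---|---|---|---|
| 0 | 0.218 | 2.9 | 170 | 50% | 162 |
| 0.1 | 0.216 | 2.0 | 105 | 19% | 44 |
| 0.2 | 0.210 | 1.1 | 31 | 4% | 2.3 |
| 0.3 | 0.199 | 0.69 | 4.9 | 0.3% | 0.9 |
| 0.5 | 0.166 | 0.34 | 1.0 | 0% | 0.4 |

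The SD hardly moves between rho 0 and 0.3, so the extreme values come from the denominator.

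**Step 2: strength read as variability.** From rho 0.3 to 0.5 the median CV falls by a factor 0.34/0.69 = 0.49. The SD of raw r accounts for 0.166/0.199 = 0.83 and the mean for 0.3/0.5 = 0.60; 0.83 x 0.60 = 0.50. Most of the fall is therefore the change in mean. The rest arises because the sampling spread of r shrinks as rho rises. The Fisher transformation removes that part: the median SD of Fisher-z FC was 0.229 at every rho.

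**Step 3: group comparison.** Two-sample t test at P<.05, 38 against 38, filtered data, untransformed CV.

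- No true difference: the CV rejected in 2.5%, 1.6%, 1.8%, 2.2% and 5.1% of runs at rho 0, 0.1, 0.2, 0.3 and 0.5. A second set of runs gave 2.5% at 0.1.
- rho 0.3 against 0.5: CV about 82-85%, SD of raw r about 75%, SD of Fisher-z FC about 5%.
- rho 0.2 against 0.3: CV about 17%. rho 0.1 against 0.2: CV about 3%, because the instability swamps the shift.

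**Step 4: the z-score.** With z = (x - m)/s and a single m and s, skewness and kurtosis of z equal those of x. They were identical before and after standardisation in every simulated map. In maps with mean rho 0 to 0.4 (SD 0.15-0.2), the top 1% of voxels carried 99-100% of the CV variance, against 9-11% for the SD.

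**The case against.** Several points on the other side stand.

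- A reader might infer that voxels with near-zero mean FC will drive spurious group differences. The simulation shows the opposite: heavy tails make the t test conservative there.
- The map figures in Step 4 describe spread across voxels within one map. A voxelwise group test depends on spread across participants at a voxel, so those figures do not measure its error rate.
- The article gives no distribution of seed-to-voxel correlations and no band for FC. Without filtering, the instability is confined to smaller rho. It also weakens if almost every voxel correlates strongly with the seed: at mean rho 0.6, SD 0.1, the top 1% carry about 57-62% of the variance.
- No group test for FC variability is stated, so any comparison is inferred. Masking or Fisher transformation may be specified in a fuller document.
- The wording "scores to enhance the normality of the data by subtracting the mean of each voxel and dividing by the standard deviation" does not settle whether standardisation is over voxels in a map or over participants at a voxel. Either way the set being standardised keeps its shape. If maps are scaled within participants, the distribution across participants can change, but nothing in the step moves it towards normality.
- A reader might also infer an error from the Introduction's report of an earlier Tuina study in terms of variance ("decreased dynamic FC (dFC) variance between the left orbital part of the middle frontal gyrus and the left fusiform"). Nothing commits this trial to that metric. The loss of comparability is a secondary remark.

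None of this rescues the CV itself. It is an explicit choice of metric, and a mask on mean FC would limit the instability but leave the confounding with strength.

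**Conclusion.** The concern holds in a limited form. Without any simulation, the CV of a signed correlation has a denominator that can be near zero or negative, it mixes strength with variability, and a linear z-score cannot enhance normality.

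Its size depends on mean FC. Near zero, the consequence is lost power, seen as null rejection of about 2-3% at a nominal 5%. The loss against a true difference in variability was not simulated and is not quantified. At moderate FC, a shift in strength from 0.3 to 0.5 is labelled a variability difference in about 82-85% of comparisons, against about 5% with the SD of Fisher-z FC.

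These figures assume Gaussian series, a constant true correlation within each scan, the ALFF band applied to FC, 38 analysed per group and a t test on untransformed CV. The scope is the dynamic FC metric only.

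**What to change.** In FC Analysis, replace the CV sentence with wording such as: *Windowed correlations will be Fisher z-transformed, and temporal variability will be the standard deviation (or variance) over windows at each voxel, standardised within each participant's brain mask before any group comparison.* Name one of the two measures. The Fisher step is needed, since the SD of raw r still rejected in about 75% of runs at rho 0.3 against 0.5.

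Delete the statement that z-scoring enhances normality; its purpose is to put participants' maps on a common scale. Keep the window length and step as they are.

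The cost is a short text change and a software setting, with no new data. The abstract reports that no data analysis had been performed, so at that stage the change could be made before any result was seen.
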